#### Muscle power and cardiorespiratory fitness

A sample size of 70 individuals (*n* = 35 per group) is also sufficient to detect a difference of 19.4% (SD 26.8%) [74] in quadriceps power (*n* = 30 per group) and to detect a relevant difference in maximal oxygen consumption (VO_2_max) of 3.5 mL/kg/min (SD 4.6 mL/kg/min) [119] (*n* = 26 per group) measured during a CPET. A difference of 3.5 mL/kg/min is associated with a 15% decrease in risk for cardiovascular disease [120]. No clinically relevant difference exists for muscle power; however, a difference of 19.4% is the minimal detectable change (MDC) from repeated testing of quadriceps peak power in older adults, as calculated by MDC = 1.96 × √2 × standard error of measurement (SEM) [74].

### Phase 2

In total, 138 individuals with COPD will be included in phase 2 (supramaximal HIT (*n* = 46), MICT (*n* = 46), and usual care (*n* = 46)). The sample size is estimated to account for an up to 30% additional drop-out rate at 24 months, in line with previous literature [121–123]. See phase 1 for complete details on the main sample size calculation. Additionally, as reported above in phase 1, the SD of 0.4 in the cognitive test battery is estimated from a trial in healthy adults comparing low to higher-intensity exercises [118] and not in patients with COPD. In phase 1, this uncertainty will be addressed with the increase in sample size from 70 to 92. However, for phase 2, we will instead perform an interim blinded sample re-estimation after half of the participants have performed baseline and 24-month follow-up, using recommended procedures for non-comparative data [124, 125], and adjust the sample size accordingly. These adaptations are recommended when there is any uncertainty in the SD. Importantly, using non-comparative data does not inflate the type I error probability or induce any bias in the treatment effect estimate (as it would if comparative data had been used) [124, 125].

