### Sample size

Sample size calculations have been made to ensure that we have a sufficient sample size to detect difference in change in all three primary outcomes for both Phase 1 and 2. For these a priori power calculations, the sample size has been determined assuming a two-sided alpha level of 0.05 and 80% power.

### Phase 1

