#### Cognitive function

Assuming an SD of 0.4, a total sample size of 60 individuals (30 per group) is needed to detect a relevant difference of 0.27 in a global cognition z-score measured using a cognitive test battery [118]. A change in *z*-score of 0.27 is clinically relevant associated with increased all-cause, respiratory, and cardiovascular mortality. To account for a drop-out rate of approximately 15% at 3 months, a total of 70 participants is necessary.

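### Phase 2: 46 per arm does not absorb the stated additional 30% drop-out; at that ceiling HIIT and MICT keep about 27 each, below the plan's own 30

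*Protocol article*

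**What the plan says.** All figures are in the protocol article, under Sample size. The opening paragraph claims enough participants "to detect difference in change in all three primary outcomes for both Phase 1 and 2", and adds that "the sample size has been determined assuming a two-sided alpha level of 0.05 and 80% power".

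Phase 1, Cognitive function, gives the base figure: "Assuming an SD of 0.4, a total sample size of 60 individuals (30 per group) is needed", for a "relevant difference of 0.27 in a global cognition z-score". It then allows for loss: "To account for a drop-out rate of approximately 15% at 3 months, a total of 70 participants is necessary". The next subsection gives 30 per group for quadriceps power (difference 19.4%, SD 26.8%) and 26 per group for VO2 (difference 3.5, SD 4.6 mL/kg/min).

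Phase 2 plans 138 people with COPD, 46 in each of HIIT, MICT and usual care. It refers back to Phase 1 for the main calculation and states: "The sample size is estimated to account for an up to 30% additional drop-out rate at 24 months". It also plans a blinded re-estimation, because the SD for cognition comes from healthy adults.

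**The concern.** The word additional places the 30% on top of the 15% already allowed at 3 months. If so, 46 per arm has to survive both losses and still leave the number the protocol calls necessary. It does not appear to.

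Phase 2 carries its own primary objective at 24 months, and the Primary outcomes section says each outcome alone can establish efficacy. If the power available is lower than the power stated, a null 24-month result would be read as stronger evidence of no difference than it is.

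**Working it through.** **Inputs, all from the Sample size section.** Two-sided alpha 0.05; power 80%; 46 per arm; 15% loss at 3 months; up to 30% further loss by 24 months. Standardised differences: cognition 0.27/0.4 = 0.675; quadriceps power 19.4/26.8 = 0.724; VO2 3.5/4.6 = 0.761.

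**1. The protocol's own evaluable numbers.** Formula: n per group = 2 × [(1.96 + 0.84) × SD / difference]², then the two-sample t version.

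| Outcome | Stated n | Normal approx. | t test |
|---|---|---|---|
| Cognition | 30 | 35 | 36 |
| Quadriceps power | 30 | 30 | 31 |
| VO2 | 26 | 28 | 29 |

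Quadriceps power reproduces by the normal approximation. VO2 is slightly low. Cognition does not reproduce: 30 per group gives 73% power by t test. That is a Phase 1 error and is kept separate from the drop-out question.

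**2. What 46 per arm leaves.**
- Sequential loss: 46 × 0.85 × 0.70 = 27.4
- Rates added: 46 × (1 − 0.45) = 25.3
- 30% as total loss: 46 × 0.70 = 32.2

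Holding the protocol's own 30 under sequential loss would need 30 / (0.85 × 0.70) = 50.4, so 51 per arm. Put the other way, 46 × 0.85 = 39.1 remain after the first loss, and 30 / 39.1 = 0.767. So 46 keeps 30 only if the further loss is at most about 23%.

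**3. By arm.** The chain of 15% then 30% fits HIIT and MICT. Under Trial design, usual care is assessed only at baseline and 24 months, so the 3-month loss need not apply to it. With 30% alone it keeps about 32.

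**4. Power at those numbers** (unadjusted two-sample t test, two-sided 0.05, no multiplicity adjustment).

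| Contrast and reading | n per arm | Cognition | Quadriceps power | VO2 |
|---|---|---|---|---|
| HIIT v MICT, sequential | 27 v 27 | 68% | 74% | 78% |
| HIIT v MICT, rates added | 25 v 25 | 65% | 71% | 75% |
| Exercise arm v usual care | 27 v 32 | 72% | 78% | 82% |
| Any pair, 30% as total | 32 v 32 | 76% | 81% | 85% |

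**5. Cognition difference detectable with 80% power.** About 0.31 at 27 per arm, 0.32 at 25 and 0.285 at 32, against the planned 0.27.

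**The case against.** The strongest reply is that 30% is the total loss by 24 months. Then 32 per arm remain, above all three stated requirements (30, 30 and 26), and quadriceps power and VO2 exceed 80%. That stands as arithmetic, but it sets aside the word additional. Even then, cognition has only 76%, so the claim for all three outcomes still fails. That failure comes from the low Phase 1 figure, not from the drop-out allowance.

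Second, 30% is an upper bound. True: 27 is the yield at the ceiling, not the expected yield. But the protocol says the sample accounts for loss up to that bound.

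Third, the protocol has safeguards. Participants who stop training are kept for follow-up where possible, so drop-out need not mean a missing outcome. Analysis is by intention to treat with multiple imputation, using ANCOVA. These may recover some power, and the figures above ignore them. However, the section on covariates says the gain from adjustment was not counted in the sample size. The blinded re-estimation may change the number enrolled, but it is tied to uncertainty in the SD, not to attrition.

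A reader might go further in four ways that the documents do not support:
- That every arm falls to 27. Usual care may keep about 32.
- That all three outcomes are underpowered on every reading. At 32 per arm, two of the three pass.
- That the whole gap to 80% for cognition is due to drop-out. At the protocol's own 30 the power is already 73%; going from 30 to 27 costs about 5 percentage points.
- That 46 was obtained by multiplying 35 by 1.3 (45.5) instead of dividing by 0.7 (50). The numbers fit, but the derivation is not given, so this is only a possible explanation.

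**Conclusion.** The statement that 46 per arm accounts for a further 30% loss is wrong as written. On the protocol's own rates, HIIT and MICT each end about 3 short of the protocol's own 30 for cognition and quadriceps power. For HIIT versus MICT, the randomised contrast in Phase 2, all three primary outcomes fall below the stated 80%: by about 12 points for cognition, 6 for quadriceps power and 2 for VO2. Against usual care, VO2 holds, quadriceps power is marginally short and cognition is about 8 points short.

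This rests on three assumptions: additional means on top of the 15%; loss reaches the 30% ceiling; and drop-outs contribute no 24-month outcome. Relaxing any of them narrows the shortfall. Reading 30% as total leaves cognition as the only outcome below 80%.

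**What to change.** In the Phase 2 sample size paragraph, and correspondingly in the SAP:
1. Withdraw or correct the statement that 46 per arm accounts for the additional 30%, and say whether 30% is additional to the 15% or the total at 24 months.
2. Give expected evaluable numbers by arm. On the additional reading this is about 27 for HIIT and MICT (25 if the rates are added) and about 32 for usual care; on the total reading it is about 32 in each arm.
3. Restate power and detectable difference for each contrast and each primary outcome. For cognition in HIIT versus MICT, the detectable difference is about 0.31 (range 0.285 to 0.32).
4. State that the blinded re-estimation addresses the SD and not attrition, and that the gain from covariates is not counted.
5. Correct the Phase 1 cognition figure (35 to 36 needed, 30 stated) as a separate item, so that the two causes are not merged.

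The cost is wording and a less favourable stated power. No increase in enrolment is asked for.

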### Allocation, randomization, and masking

In phase 1, participants will be randomized to either interventional arm or control arm with a 1:1 allocation ratio, using a computer-generated (Sealed Envelope Ltd., London, UK) blocked randomization schedule with varying block sizes of two or four, stratified by sex (male, female) and centre with equal allocation to all trial arms. For phase 2, only the participants with COPD will continue the maintenance program in their allocated group.

Group allocation will be performed after participants have been recruited into the trial; baseline assessments have been completed and eligibility confirmed. The allocation sequence will be kept in an opaque, tamper-proof sealed, and stapled envelope that will be concealed until the end of the outcome assessment. By using aluminium foil inside the envelope, it will be impermeable to intense light. A delegated person independent from enrolment, assessments, and training will generate the allocation sequence, enrol participants, and assign participants to interventions.

Outcome assessors and data analysts will be masked to group allocation. Participants will be instructed not to reveal their group allocation to the outcome assessor during interim-, 12-week, and 24-month trial assessments. In case of failure of keeping the outcome assessor masked, a second outcome assessor will be available. Given the nature of the interventions, neither participants nor instructors of the training sessions can be masked during the intervention. Hypotheses of the trial will not be revealed to the participants during their participation.

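### Phase 1 cognition needs 35–36 per group, not 30, so most of the step from 70 to 92 repairs that shortfall; with 15% drop-out and no covariate gain, 92 holds 80% power only up to SD 0.42

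*Protocol article*

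**What the plan says.** In the Protocol article, the Sample size section sets the frame: "the sample size has been determined assuming a two-sided alpha level of 0.05 and 80% power". Under Phase 1, Cognitive function, it gives the base: "Assuming an SD of 0.4, a total sample size of 60 individuals (30 per group) is needed to detect a relevant difference of 0.27". It then inflates for loss: "To account for a drop-out rate of approximately 15% at 3 months, a total of 70 participants is necessary".

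The Phase 2 paragraph of the same section admits where the SD comes from: "the SD of 0.4 in the cognitive test battery is estimated from a trial in healthy adults comparing low to higher-intensity exercises", and not from people with COPD. For Phase 1 it offers one remedy: "In phase 1, this uncertainty will be addressed with the increase in sample size from 70 to 92". For Phase 2 it plans a blinded re-estimation of the sample size instead. It does not say which SD the 92 is meant to cover.

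The 92 are split equally, 46 to HIIT and 46 to MICT. Under Statistical methods – outcomes, the Phase 1 primary analysis has one model for COPD and a separate one for healthy controls, so 92 is the number that counts for the COPD comparison.

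**The concern.** A reader who sees 70 raised to 92 takes the extra 22 as a cushion of about 31% (22/70) against an SD that may be larger in COPD. That holds only if 70 was already enough at SD 0.4, and it was not.

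Global cognition is one of three primary outcomes, each declared sufficient on its own to establish efficacy. Phase 1 has no variance check of its own; the step to 92 is given as the reason it can do without one. If the SD in COPD is moderately above 0.4, the HIIT versus MICT comparison on cognition could fall below the planned 80% power while readers believe that risk had been dealt with. A null result could then be over-read.

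**Working it through.** **Inputs, all from the Protocol article, Sample size.** Difference d = 0.27; SD = 0.4; two-sided alpha 0.05 (z = 1.960); power 80% (z = 0.842); drop-out 15%; 46 per COPD arm; 1:1 allocation; no covariate gain counted (Multicentre trial and covariates).

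**1. The protocol's base of 30 per group.** Normal approximation, n per group = 2(1.960 + 0.842)² SD²/d²:
- 2 × 7.849 × 0.16/0.0729 = 34.5, so 35 per group. The t-test (noncentral t) gives 36.
- One-sided testing gives 28, but the protocol states two-sided.
- As a check on the method, the same formula applied to the quadriceps inputs (19.4%, SD 26.8%) gives 30 per group, as printed.

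The 30 for cognition is not reproduced. At 30 per group and SD 0.4, power is 73% (t-test) or 74% (normal). Thirty would suffice only up to SD 0.367 (t-test) or 0.373 (normal).

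**2. The drop-out step.** 60/0.85 = 70.6, or 71 against the stated 70, so this step is essentially right. From the correct base:
- 70/0.85 = 82.4, so 83 randomised (normal).
- 72/0.85 = 84.7, so 85 randomised (t-test).

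The normal-approximation requirement *before* drop-out, 70 in total, happens to equal the protocol's figure *after* drop-out.

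**3. How the step from 70 to 92 is used.** 92 − 70 = 22 added. Of these, 83 − 70 = 13 to 85 − 70 = 15 are needed at SD 0.4 itself. That leaves 92 − 85 = 7 to 92 − 83 = 9 as protection against a larger SD.

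**4. What 92 covers.** 92 × 0.85 = 78, or 39 per arm. The largest SD that keeps 80% power is d√(n/2)/(1.960 + 0.842):
- 39 per arm: 0.27 × √19.5/2.802 = 0.426 (normal); 0.420 by t-test, and 0.420/0.40 = 1.05.
- 46 per arm, no drop-out: 0.462 (normal); 0.457 (t-test).
- If 30 per group had been right: 0.4 × √(39/30) = 0.456.

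**5. Power at 39 per arm, d = 0.27, unadjusted.** SDs above 0.40 are assumptions, since the documents give no COPD value.

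| SD | t-test | normal |
|---|---|---|
| 0.40 | 84% | 85% |
| 0.42 | 80% | 81% |
| 0.45 | 74% | 75% |
| 0.50 | 65% | 66% |

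**The case against.** **The 0.42 is conditional.** It assumes the full 15% loss and an unadjusted test. The protocol tries to retain participants who stop training, and it analyses everyone randomised with multiple imputation. Imputation does not restore full information, so before any covariate gain the fair range is 0.42 to 0.457. This stands, and the conditions belong in any restated sentence.

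**The planned ANCOVA should help.** It adjusts for baseline, age, sex, centre and VO2peak. If the covariates correlate 0.3 or 0.5 with the outcome (assumed; the documents give no value), the limit of 0.420/√(1 − r²) becomes 0.44 or 0.49. This also stands as a possibility. But the protocol says it left the gain out because its size is uncertain, and whether the 0.4 is already an adjusted SD cannot be told from the document. The gain therefore supports neither the 30 nor the sentence about 92.

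**On the authors' premise the step was sensible.** If 30 were right, 39 completers per arm would give a 14% margin in the SD. That is true, and it places the error in the base rather than in the idea of adding participants.

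**A reader might infer double counting.** The Phase 2 paragraph also says: "The sample size is estimated to account for an up to 30% additional drop-out rate at 24 months". The document does not support that inference. The 30% is further loss by 24 months, those participants are still present at 12 weeks, and SD uncertainty in Phase 2 is handled by re-estimation. One increase can serve both time points.

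**A reader might infer that the COPD comparison is underpowered, or that the protection is practically nil.** Neither follows. Power is 84% at SD 0.40, some margin exists, and no COPD SD is given against which to call it inadequate. Nor does the protocol promise 80% power at any particular COPD SD.

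**Conclusion.** The point holds as a sizing error with a consequence. Thirty per group does not follow from the protocol's own inputs; 35 to 36 do, or 83 to 85 randomised after 15% drop-out. The step from 70 to 92 therefore mostly makes up that shortfall. Under 15% drop-out and an unadjusted analysis, it protects 80% power up to SD 0.42, where the protocol's base would lead a reader to expect about 0.456.

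The base correction needs no outside assumption. The coverage figure rests on the stated difference, alpha, power and drop-out, and it widens with better retention or useful covariates. Whether the true COPD SD exceeds 0.42 is unknown. The error lies in what the protocol says its sample size delivers and does not show that 92 is too few.

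**What to change.** 1. Under Sample size, Phase 1, Cognitive function, replace 30 per group and 70 in total with 35–36 per group and about 83–85 randomised after 15% drop-out, and name the method used.
2. In the Phase 2 paragraph, replace the sentence on the step from 70 to 92 with its actual coverage, for example: with 39 per arm after 15% drop-out and an unadjusted test, power for a difference of 0.27 is 84% at SD 0.40, 80% at 0.42, 74% at 0.45 and 65% at 0.50; any gain from covariates is not counted.
3. Optionally, compute one blinded pooled SD of the 12-week cognition change in COPD and report the resulting detectable difference before unblinding. This leaves power unchanged but tells readers what a null result can exclude.

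The cost is a less favourable statement and, if item 3 is taken up, one calculation on data already being collected. The COPD arms need no further enrolment, since 92 exceeds 85. The corrected base will also show that the 70 healthy controls, analysed in their own model, have about 73% power at SD 0.4 after 15% loss (35 × 0.85 ≈ 30 per arm). The text should say so.

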## Methods: settings and participants

### Study setting

Phases 1 and 2 of the COPD-HIIT trial will be performed at two centres, one in Sweden: Department of Community Medicine and Rehabilitation, Physiotherapy, Umeå University, Umeå, and Norrlands Universitetssjukhus (NUS, Umeå, Sweden) (site investigators AN (principal investigator), JJ and JV) and one in Belgium: Faculty of Rehabilitation Sciences, Hasselt University, Diepenbeek, and Ziekenhuis Oost-Limburg (ZOL, Genk, Belgium) and Jessa Ziekenhuis (Hasselt, Belgium) (site investigators CB (principal site investigator), JDB, DR, and DC). Enrolment began in November 2023, and we expect recruitment in phase 1 to be completed by the end of 2026. Thus, data collection of phase 2 is expected to be completed at the end of 2028. All trial centres will have qualified personnel including a medical doctor and health care professionals with experience in working with people with COPD. Principal site investigators have a Ph.D. and research experience in the research area. Trial centre facilities possess all the relevant equipment for performing relevant assessments and interventions (as described in the ‘ Interventions’ and ‘ Outcomes’ sections).

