### Participants and recruitment

We will recruit participants with COPD via primary and specialist health care or advertisement. Matched healthy controls will be recruited via advertisement. All advertisements will have approval by the regional ethical board and will be disseminated via billboards, newspapers, local organization contacts, or targeted social media (e.g., Facebook). Each participant will receive financial compensation in an amount determined by the local centre and ethical board. If a participant would drop out, payments will be pro-rated based on the length of time stayed or the number of visits performed in the trial.

The planned distribution of participants per centre is as follows: in Umeå, approximately two-thirds (*n* = 138) of the participants will be recruited and in Hasselt the remaining third (*n* = 70) of participants. Subsequently, 92 individuals with COPD (HIIT: *n* = 31, MICT: *n* = 31, usual care: *n* = 30) and 46 HC (HIIT: *n* = 23, MICT: *n* = 23) are planned to be recruited in Umeå, while 46 individuals with COPD (HIIT: *n* = 15, MICT: *n* = 15, usual care: *n* = 16) and 24 HC (HIIT: *n* = 12, MICT: *n* = 12) are planned to be recruited in Hasselt. The enrolment period is expected to extend over approximately 24 months.

Written informed consent will be obtained by the assessors (AN, JJ, JDB, and DC) trained in Good Clinical Practice after all procedures have been explained, before the start of the trial during participants’ first test day.

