### Statistical methods

The change-from-baseline analyses will be performed after the last participant has completed all assessments of phase 1 and phase 2, respectively, after monitoring and data quality checks. Analyses will be performed blinded by the investigators supported by a biostatistician. All statistical tests will be conducted as two-sided, with the alpha level set at 0.05.

Baseline variables and descriptive statistics with continuous data will be presented with mean (SD) or median (IQR) as appropriate. Continuous data with normative values (for example, VO_2_peak and lung function values) will also be presented as % predicted value. Ordinal variables will be presented as median (IQR) or as *n* (%), and categorical variables will be presented as *n* (%).

A separate detailed SAP with further details about the statistical analyses including the method to handle family-wise error rate for the multiple primary outcomes will be published and finalized before the database is locked and randomization codes unblinded. In line with recommendations, it increases transparency and replicability and might be updated in response to new methods, challenges encountered during the trial, funding availabilities, and emerging evidence during the period of the trial [130, 131].

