## Trial status

This manuscript reports protocol version 1.1 finalized at 11 April 2024. Ethical approval has been obtained for all procedures in Umeå, Sweden, and in Hasselt, Belgium. The trial started enrolling participants on the 9th of November 2023 in Umeå, Sweden and on the 16th of September 2024 in Hasselt, Belgium. At the time of manuscript submission (3 January 2024), 14 participants had been enrolled. At manuscript acceptance, 17th September 2024, 51 participants have been enrolled. Data collection for phase 1 is expected to take place over 2–3 years, while phase 2 is expected to take place over 5 years.

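### The Phase 2 blinded sample size re-estimation is triggered after recruitment is due to close, so it cannot change the sample size within the stated timetable

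*Protocol article*

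**What the plan says.** The Phase 2 part of the Sample size section sets the size: "In total, 138 individuals with COPD will be included in phase 2", 46 per arm, with up to 30% additional loss allowed for at 24 months. It acknowledges that the SD of 0.4 for the cognitive score comes from healthy adults and not from people with COPD. Phase 1 meets that uncertainty by enlarging the sample from 70 to 92. For Phase 2 the protocol turns to a re-estimation: "we will instead perform an interim blinded sample re-estimation after half of the participants have performed baseline and 24-month follow-up". It is to be carried out "using recommended procedures for non-comparative data", after which the sample size is to be adjusted.

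The calendar is given in three places:
- Study setting: enrolment began in November 2023 and "we expect recruitment in phase 1 to be completed by the end of 2026"; Phase 2 data collection is therefore expected to end at the close of 2028.
- Participants and recruitment: "The enrolment period is expected to extend over approximately 24 months".
- Trial status: the first centre began enrolling on 9 November 2023 and the second on 16 September 2024. "At manuscript acceptance, 17th September 2024, 51 participants have been enrolled".

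On the analyses, Statistical methods says: "The change-from-baseline analyses will be performed after the last participant has completed all assessments of phase 1 and phase 2, respectively".

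**The concern.** A re-estimation is useful only if its result can still be acted on. Here it waits for 24-month outcomes in half of the sample, while recruitment is planned to last 24 to 38 months in total. By the time the SD is known, recruitment is due to have ended.

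This matters because the re-estimation is the measure that the protocol names for Phase 2 against an SD it admits is uncertain. If it cannot act, Phase 2 is in practice a fixed-size trial whose power depends on an SD borrowed from another population.

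A secondary point concerns the order of events. The last Phase 1 assessment comes before the trigger on either calendar, and the same HIIT and MICT allocation carries over into Phase 2. Those who decide on the sample size could therefore already know comparative 12-week results on the same three primary outcomes.

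**Working it through.** **Inputs.** Start 9 November 2023 (Trial status). Recruitment end: 31 December 2026 (Study setting) or about 24 months after the start, 9 November 2025 (Participants and recruitment). Phase 2 size 138, so half is 69. End of Phase 2 data: end of 2028. Assumptions: even accrual, COPD participants and controls enrolled in proportion, and 14 weeks from enrolment to the last Phase 1 assessment.

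**The protocol's own calendar.** End of 2026 + 24 months = end of 2028. This reproduces and leaves no slack: the last person recruited on time finishes on the last planned date.

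**General condition.** If enrolment lasts T months, half are enrolled at T/2 and have 24-month data at T/2 + 24. For this to precede closure, T/2 + 24 < T, so T > 48 months. The protocol gives T = 24 or T = 37.7.

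**Dates.**

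| | End-2026 calendar | 24-month calendar |
|---|---|---|
| Half enrolled | about 5 June 2025 | about 8 November 2024 |
| Trigger (+24 months) | about 5 June 2027 | about 8 November 2026 |
| Months after closure | 5.1 | 12.0 |
| Last Phase 1 assessment | about 8 April 2027 | about 15 February 2026 |
| Person added at the trigger reaches 24 months | June 2029 | November 2028 |

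If the trigger means 69 people with data in hand and 30% are lost, the share that must be enrolled is 0.5/0.7 = 71%. The trigger moves to about February 2028 (13 months after closure) or April 2027 (17 months after).

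**Room before the end of 2028.** On the end-2026 calendar anyone added finishes in June 2029 or later. On the 24-month calendar a person added on the trigger date itself would just fit, but only those enrolled by the end of 2026 would finish in time. That leaves 53 days to compute the SD, decide, and reopen recruitment that closed a year before. With 69 completers required, that window is gone.

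**Observed accrual.** A trigger by the end of 2026 needs 69 COPD participants enrolled by the end of 2024. Even accrual to the end of 2026 gives 138 × 13.7/37.7 ≈ 50. The reported 51 in 10.3 months is 4.96 per month, or about 68 by the end of 2024, healthy controls included.

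**What is at stake.** Evaluable per arm: 46 × 0.70 = 32.2, about 32. Two-sided t-test at 0.05, difference 0.27:
- SD 0.4: standardised difference 0.675, power about 76%.
- SD 0.5 (assumed): standardised difference 0.54, power about 57%.

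Needed for 80% power, n = 2 × (1.96 + 0.84)² × (SD/0.27)² = 15.7 × (SD/0.27)² per arm. SD 0.4 gives 34.5, so 35 (t-test 36). SD 0.5 gives 53.8, so 54 (t-test 55). The protocol's figure of 30 per group for cognition is smaller than this formula gives; that is a separate matter on which the timing does not depend.

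**The case against.** All dates are worded as expectations, and the Protocol amendments section lists sample size among the things that an amendment may change. The trial could therefore extend itself. This stands to the extent that the accurate claim is that the size cannot be changed without extending the stated timetable. A general amendment clause is not a plan to hold recruitment open or to lengthen follow-up.

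The end-2026 date refers to Phase 1 recruitment, and the usual care arm is not part of Phase 1. That is correct, but the end-2028 date still bounds that arm's 24-month assessment, and adding usual care participants alone would do nothing for HIIT against MICT.

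The accrual figure comes almost entirely from one centre, since the second opened the day before the count. Month-level dates are therefore illustrative. A later second centre makes accrual more back-loaded, however, and that delays the trigger.

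The plan adjusts for covariates and did not count the resulting gain. That is fair: the power figures above are unadjusted, SD 0.5 is an assumption, and the re-estimation should not be called the only safeguard.

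A reader might infer that the re-estimation cannot stay blinded and that control of type I error fails. The documents do not support this. A pooled SD of 24-month change needs no allocation codes and stays non-comparative even if 12-week results are known. Statistical methods describes blinded analysis and does not say when the Phase 1 codes are opened. On the end-2026 calendar only about two months separate the last Phase 1 assessment from the trigger, so a finished Phase 1 analysis is an inference. What remains is narrower: those setting the size might know 12-week comparative results, and the article describes no separation. The SAP, which is not shown, may do so.

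**Conclusion.** The timing defect holds on the protocol's own figures. Under even accrual the trigger falls about 5 months after closure on the end-2026 calendar and about 12 months after on the 24-month calendar, and later if 69 completers are required. The re-estimation then needs recruitment to be reopened. It also needs follow-up past the end of 2028: certainly on the end-2026 calendar, and for all but a nominal 53-day window on the 24-month one. The protocol provides for neither.

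Unless that changes, Phase 2 has about 76% power at SD 0.4 and about 57% at the assumed SD of 0.5, before any covariate gain. Exact dates depend on the accrual pattern; the direction would reverse only with strongly front-loaded enrolment, which the reported count does not show. Possible prior knowledge of Phase 1 results is a secondary point about who decides and when, not a finding that the blinding is broken.

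**What to change.** Reconcile the trigger with the recruitment dates in Study setting and in Participants and recruitment, which also need to agree with each other. Then choose one of two routes.

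1. If recruitment is still sufficiently open, base the blinded re-estimation on the pooled SD of 12-week change in the randomised COPD participants, once half of them have 12-week data and before any Phase 1 codes are opened. With even accrual and 14 weeks to assessment, this falls about September 2025 on the end-2026 calendar, some 15 months before closure. State in advance an allowance for a larger 24-month SD.
2. If recruitment is too advanced, delete the re-estimation and present Phase 2 as fixed-size, with power restated over a range of SDs.

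Under the first route, also state who performs the calculation and that it precedes the opening of the Phase 1 codes.

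The cost is an amendment and, for the first route, one blinded SD calculation. That route has a real limit. The usual care arm is assessed only at baseline and 24 months, so a 12-week SD contains nothing from one of the three arms, and it may understate the 24-month SD. The existing trigger does measure the right quantity in all three arms, but too late to use it.
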